5.1.1 Trial Design

Subjects will be screened up to thirty (-30) days in advance of study enrolment, and will demonstrate a satisfactory baseline medical assessment by history, physical examination, haematological and biochemical analysis (stable health status with no exclusionary medical or psychiatric conditions). Forty-eight (48) study subjects will be randomized into 4 treatment groups of 12, described in Table 4 below:

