**Table 4 Study Design**

| ***Test Material*** | ***Treatment Group*** | ***No. of Subjects*** | ***Dose Level*** | ***Administered on Day*** |
| --- | --- | --- | --- | --- |
| Plant-based H5 VLP (H5N1) pandemic influenza vaccine combined with Alhydrogel® 1% | Treatment Grp 1 | 12 | 5 µg | 0 / 21 |
| Plant-based H5 VLP (H5N1) pandemic influenza vaccine combined with Alhydrogel® 1% | Treatment Grp 2 | 12 | 10 µg | 0 / 21 |
| Plant-based H5 VLP (H5N1) pandemic influenza vaccine combined with Alhydrogel® 1% | Treatment Grp 3 | 12 | 20 µg | 0 / 21 |
| 100mM phosphate buffer + 150 mM NaCl + 0.01% Tween 80 combined with Alhydrogel®1% | Treatment Grp 4 (Placebo) | 12 | N/A | 0 / 21 |

The first cohort will consist of sixteen subjects; 12 subjects will be randomized to receive a 5µg dose of plant-based H5 VLP (H5N1) pandemic influenza vaccine and 4 subjects will be randomized to receive the placebo preparation. A telephone call to obtain safety data and to remind study subjects to continue completing the Memory Aid will be made at Day 1 (~24 hours post vaccination). Eight (8) days following each vaccination, subjects will be telephoned by clinic staff to review and record safety data. Seven-day (7) safety data for subjects in the first cohort will be tabulated and reviewed by the Investigator and 2 medical advisors, prior to permitting the second cohort to receive a higher dose (10µg) of study vaccine. The same procedure will be repeated with the second cohort of sixteen subjects. Following a favourable review of the second cohort’s seven-day safety data by the medical advisors, cohort 3 subjects will be permitted to be randomized to the highest dose level (20µg). There will be a total of four (4) seven-day safety reviews by the Investigator and medical advisors.

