5.1.2 Trial Design and Plan

Subjects will be enrolled in the study in a staggered fashion. Refer to Figure 2 below. Study enrolment will begin with two (2) subjects from Cohort 1 on Day 0; one subject will be randomized to receive the 5µg dose of plant-based H5 VLP (H5N1) pandemic influenza vaccine combined with Alhydrogel® intramuscularly and one subject will be randomized to receive the placebo preparation, 100mM phosphate buffer + 150mM NaCl + 0.01% Tween 80 combined with Alhydrogel®. Subsequently, the following day, 3 subjects will be randomized to receive H5 VLP (H5N1) pandemic influenza vaccine and 1 subject will be randomized to receive the placebo preparation. On Day 2 of the study, 4 subjects will be randomized to receive H5 VLP (H5N1) pandemic influenza vaccine and 1 subject will be randomized to receive the placebo preparation. On Day 3 of the study, 4 subjects will be randomized to receive H5 VLP (H5N1) pandemic influenza vaccine and 1 subject will be randomized to receive the placebo preparation, for a total Cohort of 16 subjects. Once all Cohort 1 subjects have completed Day 7, a blinded safety report will be generated and reviewed by a panel consisting of the Investigator and two independent, expert medical advisors. A favourable 7-day safety report will permit the initiation of the vaccination of Cohort 2 at the 10µg dose level. A second blinded safety report will be conducted following the second vaccination at the 5µg dose level. A blinded seven-day safety report evaluating the safety of subjects receiving the 10µg dose will be generated in the same manner, in addition to a safety report being generated seven days following the second 10µg dose of study vaccine. Study vaccine dose escalation to 20µg will only be permitted if safety data is favourable, as judged by the Investigator and medical safety experts. Safety reports will be generated following the first and second dose of vaccine at the 5 µg and 10µg dose levels, and after the first dose of the 20µg dose level is completed, for a total of 5 reports.

The proposed randomization schedule is described below.

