**Attn: [name]**

6.6 Randomization/Allocation Procedures

The site will be provided a pre-determined sequence of randomization numbers according to the randomization code. Potential study subjects will be screened in a sequential fashion. Once screening is completed and study eligibility is confirmed, the randomization numbers of the pre-determined sequence will be allocated sequentially to subjects within the appropriate treatment group. Once a randomization number has been assigned, it will not be re-used in any event. No subjects will be entered into the study more than once. If a randomization number has been allocated incorrectly, no attempt will be made to remedy the error once study vaccine has been dispensed. The subject will continue with the randomization number and study vaccine. The study staff will notify the Sponsor as soon as the error is discovered without disclosing the study vaccine administered. Admission of subsequent eligible subjects will continue using the next unallocated number in the sequence.

Once it is determined that a study subject is eligible for randomization, a three-digit randomization number, (e.g. 101, 102, 103) and treatment will be assigned. This randomization number and treatment will be recorded along with the two-digit screening number for each subject on the Study Vaccine Accountability Log.

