6.7 Blinding and Code Breaking Procedures

The randomization code will not be broken except in emergency cases wherein the identification of the treatment is necessary for appropriate treatment of the subject. A sealed envelope containing the un-blinded randomization schedule may be kept in a locked, secured location at the clinical site. In such circumstances, the un-blinded randomization code may be opened with the permission of the Sponsor Medical Monitor and the treatment assignment would be revealed.

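### The only code-break device named in Section 6.7 is one optional envelope holding the randomization schedule, so a break for one subject shows its reader every assignment on that schedule

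*Protocol*

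**What the plan says.** Protocol Section 6.7 keeps the code closed "except in emergency cases wherein the identification of the treatment is necessary for appropriate treatment of the subject". The condition concerns one person. The device is described in one sentence: "A sealed envelope containing the un-blinded randomization schedule may be kept in a locked, secured location at the clinical site". Its use follows: "the un-blinded randomization code may be opened with the permission of the Sponsor Medical Monitor and the treatment assignment would be revealed". The last phrase is singular, so disclosure of one assignment is evidently intended. No envelope or code for a single subject or a single cohort is described anywhere in the protocol.

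Section 6.6 describes the list: "The site will be provided a pre-determined sequence of randomization numbers according to the randomization code". On its use it adds that "the randomization numbers of the pre-determined sequence will be allocated sequentially to subjects within the appropriate treatment group". Each subject's number and treatment are also entered on the Study Vaccine Accountability Log.

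Enrolment is staged. Section 5.1.1 gives the total: "Forty-eight (48) study subjects will be randomized into 4 treatment groups of 12". The text under Table 4 gives the cohort: "The first cohort will consist of sixteen subjects; 12 subjects will be randomized to receive a 5µg dose", with 4 more on placebo. Section 5.1.2 fixes the mix for each enrolment day, for example "On Day 2 of the study, 4 subjects will be randomized to receive H5 VLP (H5N1) pandemic influenza vaccine and 1 subject will be randomized" (that last subject being the day's placebo recipient). Cohorts 2 and 3 each open only after a favourable review of blinded seven-day safety data from the cohort before.

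**The concern.** The purpose and the tool in Section 6.7 do not match. The purpose is to learn one subject's treatment. The tool discloses a list. Permission from the Medical Monitor governs when the envelope is opened, but not how much it shows.

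Two things are at stake. The first is allocation concealment: numbers are issued in a fixed order, so anyone who has seen a list covering later subjects knows the next subject's arm. The second is the assessors' blind. Section 6.3.2 leaves the dose level open to clinic staff, so vaccine versus placebo within a cohort is the comparison the blind protects. The primary endpoints in Section 8.1.1.1 are largely graded symptoms and their relationship to vaccination. Clinic staff record the symptoms by telephone (Section 5.1.5.4). The investigator judges causality (Section 9.1.6) and also sits on the panel that reviews blinded data before each escalation (Section 5.1.2). One of the possible stopping criteria in Section 9.1.8 depends on an attribution to the study vaccine.

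**Working it through.** The protocol gives no figure for what a code break exposes, so the check is a count.

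**Inputs**
- Daily enrolment per cohort (Section 5.1.2, Figure 2): vaccine 1, 3, 4, 4; placebo 1, 1, 1, 1.
- Cohorts: 3 (Section 5.1.1, Figure 2).
- Timing in Figure 2: cohort 1 on Days 0 to 3; cohort 2 starts about Days 10-12 and is filled about Day 15; cohort 3 starts about Days 22-24 and is filled about Day 27; cohort 3's second dose falls on Days 45 to 48.

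**Totals.** Vaccine 1 + 3 + 4 + 4 = 12; placebo 4; cohort 12 + 4 = 16; trial 3 × 16 = 48. This agrees with 4 groups of 12.

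**Assignments shown beyond the one needed**
- One trial-wide schedule: 48 − 1 = 47.
- A separate schedule per cohort: 16 − 1 = 15.

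**Of these, subjects not yet enrolled (trial-wide schedule)**

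| Time of break | Already enrolled, other than the index subject | Not yet enrolled |
| --- | --- | --- |
| Cohort 1 filled, cohort 2 not started (about Day 3 to Days 10-12) | 16 − 1 = 15 | 48 − 16 = 32 |
| Cohort 2 filled, cohort 3 not started (about Day 15 to Days 22-24) | 32 − 1 = 31 | 48 − 32 = 16 |
| Cohort 3 filled (after about Day 27) | 48 − 1 = 47 | 0 |

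With a schedule per cohort, concealment is exposed only during that cohort's own four enrolment days: 14, 10, 5 and 0 subjects remain after each day (16 − 2, 14 − 4, 10 − 5, 5 − 5).

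**How long the assessors' blind matters.** Solicited symptoms are collected for 7 days after each dose, so the last are due about Day 48 + 7 = Day 55. Adverse event and causality assessment continue to Day 228.

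**What a code per subject would still reveal.** The daily mix is known and the day-groups have 2, 4, 5 and 5 subjects. If the index subject is on placebo, the other 1, 3, 4 or 4 subjects of that day must be on vaccine. If the index subject is on vaccine, nothing certain follows about the others, except on a cohort's first day: that group is one vaccine and one placebo, so opening either code reveals the other. The remaining leakage is therefore at most 1 to 4 subjects, against 47 or 15.

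**The case against.** **The text does not fix how much the schedule covers.** Section 6.7 does not say that it spans all three cohorts, and the reference in Section 6.6 to allocation within a treatment group is compatible with separate lists. This stands: exposure of all 48 is conditional. A split list still shows 15 assignments too many.

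**The envelope is optional and other information is on site.** It only may be kept, the accountability log records treatment per subject, and an un-blinded staff member gives the injections (Section 6.2.2). This is true, but neither the log nor that person is named as a code-break route. Without the envelope, Section 6.7 describes no device at all.

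**Loss of the raters' blind does not follow automatically.** A reader might infer that one break tells the whole site every subject's arm to the end of the study. The protocol does not support that, because it does not say who opens or reads the envelope. It is a possibility, not a consequence.

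**Timing limits the harm.** A reader might also take 32 unenrolled subjects to apply to any break during cohort 1's follow-up. It applies only until cohort 2 starts. After about Day 27 there is no later enrolment to protect, and after about Day 55 no solicited symptoms are left to collect.

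**The event is unlikely.** Participants are healthy adults. One could assume a chance of 0.1% to 1% per subject of needing a break, giving 1 − 0.999^48 = 4.7% to 1 − 0.99^48 = 38% for at least one. The protocol gives no such rate, and the sum counts late breaks the same as early ones, so the point does not rest on it.

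**Another route to un-blinding exists.** Sections 5.1.1 and 9.1.8 let reviewers un-blind the seven-day safety data on their medical judgement. Changing the envelope does not touch that route.

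**Conclusion.** The point holds as a weakness in a stated procedure. Carried out as written, a permitted break for one subject shows the reader of the envelope 47 further assignments if the schedule is trial-wide, or 15 if it is split by cohort. Under a trial-wide list, 32 of these belong to subjects not yet enrolled if the break falls between cohorts 1 and 2, 16 if it falls between cohorts 2 and 3, and none after about Day 27. A later break can still affect symptom recording to about Day 55, and adverse event and causality assessment to Day 228, provided that blinded assessors see the list.

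This rests on the schedule's coverage, which Section 6.6 suggests but does not settle, and on the approximate days in Figure 2. It does not show that the blind will be lost, and it puts no probability on a break. The change is still worth making: a blind once lost cannot be restored, and prevention costs almost nothing.

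**What to change.** In Section 6.7, replace the single envelope with one sealed code per randomization number, marked with that number and showing only that subject's treatment. Require the date and reason to be recorded at each opening. State that the full schedule is held only by un-blinded personnel who do not assess subjects.

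The cost is the preparation of 48 envelopes and a few lines of text. Emergency access is unchanged. The same-day leakage of at most 1 to 4 subjects remains, because Section 5.1.2 publishes each day's mix. The reviewers' option to un-blind the seven-day safety data is a separate matter that this change does not address.

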6.8 Concomitant Therapy

Subjects should be instructed not to introduce any new medications without consulting or notifying the Investigator or designee. Any new or changed medications reported by the subject post vaccination and through the Day 42 visit, will be recorded. Since AEs may be secondary to new medications, interviewers will explore the reasons for the new medications and document these AEs. Concomitant medications will include prescription and over-the-counter drugs, vitamins, herbal products and nutritional supplements (any product viewed by the subject as distinct from food). Investigators and other study staff are encouraged to capture the most detailed description of vitamins, herbals, and supplements possible, as otherwise these products may be difficult to classify.

7.0 SPECIMENS AND CLINICAL SUPPLIES

7.1 Management of Samples

Screening blood samples for biochemistry and haematology; urinalysis and urine for pregnancy testing will be performed. Biochemistry, haematology sampling as well as urinalysis will be repeated at Day 21 and Day 42. Serology samples for immunogenicity analysis will also be taken. Refer to the Study Laboratory Manual for complete information on the handling and shipment of all laboratory samples.

7.1.1 Sample Collection

Blood samples will be collected for screening haematology as follows: haemoglobin, hematocrit (packed cell volume, PCV, red blood cells, platelets, mean cell haemoglobin (MCH), mean cell concentration (MCHC), mean cell volume (MCV), white cell count (total, WBC), neutrophils, lymphocytes, monocytes, eosinophils, and basophils. The following biochemistry tests be will conducted: sodium, potassium, urea, creatinine, glucose, alkaline phosphatase, alanine transferase (ALT), serum glutamate pyruvate transaminase (SGPT), bilirubin, albumin, urate, aspartate transferase (AST, SGOT), gamma glutamyl transferase (GGT), chloride, cholesterol and triglyceride. Urinalysis testing will include pH, specific gravity, glucose, protein and blood. A pregnancy urinalysis will also be conducted. Refer to the study Laboratory Manual for further information.

Four (4) samples for serological analysis will be collected from each study subject (~10mL each time or 2X clot-tube or red stopper). HAI antibody titres will be determined based on sera drawn immediately prior to administration of the first dose of study vaccine. Twenty-one (21) days later, prior to administration of the second dose of vaccine, a serology sample will be drawn. Serology samples will also be drawn at the time of the Day 42 visit and the final visit on Day 228. Should a subject be discontinued from the study, a sample will be drawn at the time of the final safety visit. Four (4) samples for cell-mediated assays will also be collected from each study subject (~2mL or 4X 5mL EDTA tube) prior to the first immunization and at Days 21, 42 and 228. These samples will be cryopreserved on the day of collection and held for later testing.

7.1.2 Sample Preparation

Preparation of the laboratory samples for the collection and shipping of biochemistry, haematology and urinalysis will be described in the Study Laboratory Manual.

Ship samples to Laboratory on the day of collection. Label each tube with the label provided and complete the subject ID number, date, visit #.

Blood samples for serology will be collected in one (1)10mL serum separator tube. The samples will be kept at room temperature for a maximum of 30 minutes and stored in the fridge for a maximum 24 hours until centrifuged at the appropriate speed (1200g) for 10 minutes at 4ºC or for five (5) minutes at ambient temperature. Serum will be divided into 4 aliquots into 4 separate polypropylene tubes as soon as possible: two of at least 0.5mL (when possible) and the other two containing equal amounts of the remainder of the serum (when possible).

Medicago R&D Inc. will measure HAI titres in serum samples using a validated method. Serum samples from subjects who do not complete the study through Day 42, due to adverse events, lost to follow-up or insufficient amount of serum will be analyzed and reported, but the results will not be used for the study analysis.

Samples for cell-based assays will be shipped at room temperature to [name] laboratory at the MUHC-RI to arrive within 4 hours of collection (Attention [name], R3-103, Montreal General Hospital, [name]). There, peripheral blood mononuclear cells will be isolated and cryopreserved in 2-4 aliquots (depending upon cell counts) at ~5x10^6^ cells/mL. These cells will be held in liquid N vapour until used.

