11.0 STATISTICAL METHODS AND DETERMINATION OF SAMPLE SIZE

11.1 Statistical Methods

Data analysis will be performed at Anapharm Inc.

An interim clinical study report analyzing safety and immunogenicity at 42 days post-vaccination will be completed.

All descriptive and inferential statistical analyses will be performed using SAS^®^ Version 8.2 or higher statistical software. Descriptive statistics for continuous variables will consist of the mean, median, geometric means (where appropriate), standard deviation, minimum, and maximum values. For categorical variables, the number and percent of each category will be displayed. Frequency tables for categorical variables may be performed using Microsoft^®^ Office Excel 2003 or higher version.

For the analysis of safety and immunogenicity endpoints, a two-sided alpha level of 5% will be used. All statistical tests will be two-tailed unless otherwise stated. No attempt will be made to control type I error rate inflation attributable to multiple comparisons.

Demography will be compared among treatment groups using Fisher’s exact test for categorical factors and the Kruskal-Wallis test for continuous factors.

The calculations and statistical analyses will be further described in a statistical analysis plan.

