11.2.1.2 Full Analysis (Intent-to-Treat) Immunogenicity Population

The Full Analysis Set will consist of the subset of the Safety Set with a Day 0 and any post-vaccine immunogenicity assessment. Subjects who received the wrong treatment will be analyzed as randomized.

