11.2.1.3 Per-Protocol Immunogenicity Population

The Per Protocol Set will consist of the subset of the Full Analysis Set who completed the study with no major protocol violation. For the Day 21 analysis, this should include the subjects who received the first vaccine dose and had Day 0 and Day 21 immunogenicity measurements. For the Day 42 analysis this should include the subjects who received both vaccine doses and had Day 0 and Day 42 immunogenicity measurements.

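### Section 7.1.2 keeps the Day 21 titres of subjects who leave between Day 21 and Day 42 out of the analysis, while section 11.2 includes them

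*Protocol*

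**What the plan says.** Section 7.1.2 of the Protocol (Sample Preparation) contains an exclusion rule for HAI results. The sentence opens "Serum samples from subjects who do not complete the study through Day 42, due to adverse events, lost to follow-up or" and ends "insufficient amount of serum will be analyzed and reported, but the results will not be used for the study analysis". It has no exception for the Day 21 analysis.

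Section 11.2 defines the analysis sets differently.

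- Section 11.2.1.2: "The Full Analysis Set will consist of the subset of the Safety Set with a Day 0 and any post-vaccine immunogenicity assessment".
- Section 11.2.1.3, opening sentence: "The Per Protocol Set will consist of the subset of the Full Analysis Set who completed the study with no major protocol violation".
- Section 11.2.1.3, next sentence: "For the Day 21 analysis, this should include the subjects who received the first vaccine dose and had Day 0 and Day 21 immunogenicity measurements". The sentence after that requires both doses and a Day 42 titre, but only for the Day 42 analysis.

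The Synopsis repeats the completion requirement for the Per Protocol Set without the visit-specific sentences. Section 11.2.2 makes the Per Protocol Set the primary set for immunogenicity and leaves use of the Full Analysis Set to need. Section 11.1.2.1 plans formal comparisons at both Day 21 and Day 42. Section 7.1.1 has the Day 21 serum drawn before the second dose.

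**The concern.** Two analysts who follow different sections would analyse different people at Day 21. That choice should be settled before any titre is seen.

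The 7.1.2 version also carries a risk of bias. The Day 21 titre is complete when the blood is drawn, and nothing that happens afterwards can make it invalid. A rule that removes it because the subject left later selects on an outcome after vaccination. Adverse events are one of the named reasons and may depend on vaccine and dose, so the selection could differ between a vaccine group and placebo.

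The completion wording in 11.2.1.3 and the Synopsis adds a smaller difficulty. It sits badly with the visit-specific sentences that follow it in 11.2.1.3, and in the Synopsis nothing corrects it.

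**Working it through.** **The plan's own figures.** Section 11.3 gives only safety detection probabilities for 12 subjects per group. With 1 − (1 − p)^12, p = 0.10 gives 71.8% (stated: about 72%) and p = 0.05 gives 46.0% (stated: about 46%). Both are reproduced and neither is in dispute. The Protocol states no dropout rate and no expected immune response.

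**The rules side by side.** Take a subject with dose 1 and valid titres at Day 0 and Day 21, who is lost to follow-up on Day 30 with no major violation.

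| Rule | Day 21 titre used? |
| --- | --- |
| 7.1.2 | No |
| 11.2.1.2, Full Analysis Set | Yes |
| 11.2.1.3, Day 21 sentence | Yes |
| 11.2.1.3 opening sentence, and Synopsis | No, if read alone |

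**Who is affected.** A subject who leaves before Day 21 has no Day 21 titre under any rule. A subject who leaves before Day 42 generally has no Day 42 titre either. So the conflict changes the Day 21 result, through subjects who leave between Day 21 and Day 42.

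**How often (assumed rates).** Let d be the chance that a subject with a Day 21 titre then leaves before Day 42 for a named reason. The chance that a group of 12 loses at least one is 1 − (1 − d)^12: 22% at d = 2%, 46% at 5%, 72% at 10% and 86% at 15%.

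**Bias (assumed rates).** With true seroprotection p, and dropout d_r in responders and d_n in non-responders, the retained proportion is p(1 − d_r) / [p(1 − d_r) + (1 − p)(1 − d_n)]. At p = 0.60:

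- d_r = d_n = 5%: 0.57 / (0.57 + 0.38) = 60.0%, no bias.
- d_r = 5%, d_n = 15%: 0.57 / (0.57 + 0.34) = 62.6%.
- d_r = 15%, d_n = 5%: 0.51 / (0.51 + 0.38) = 57.3%.

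**Precision.** The 95% half-width for a mean log titre, in SD units, is t(0.975, n − 1)/√n: 0.635, 0.672, 0.715 and 0.769 for n = 12, 11, 10 and 9. Losing one, two or three of 12 widens the interval by 6%, 13% or 21% at the same SD.

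**One exclusion and the planned test** (Fisher's exact, two-sided 5%, placebo 0/12):

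- 4/12: the observed table has probability C(12,4)/C(24,4) = 495/10626 = 0.0466. The opposite extreme is equally likely and is added, so p = 0.093.
- 4/11, one non-responder removed: C(11,4)/C(23,4) = 330/8855 = 0.0373. The opposite extreme, 495/8855 = 0.0559, is more likely than the observed table and is not added, so p = 0.037.
- 3/11, one responder removed: C(11,3)/C(23,3) = 165/1771 = 0.0932. The opposite extreme, 220/1771 = 0.124, is not added, so p = 0.093.

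Part of the drop to 0.037 comes from the way the two-sided test treats unequal groups. The example shows that the result is fragile, not how large the bias is.

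**The case against.** The best defence is that 7.1.2 is one sentence in a sample-handling section, while 11.2 is the section that defines populations and a sensible analyst would follow it. It concerns a secondary endpoint in a 48-subject Phase 1 trial, and the statistical analysis plan, which is not at hand, may settle the matter. This bears on how serious the point is. It does not remove the contradiction: 7.1.2 is a plain instruction about what enters the study analysis, and nothing in the Protocol ranks it below 11.2.

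A reader might infer more than the documents support.

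- *That the titres are thrown away for anyone who leaves.* The samples are still assayed and reported. Section 7.1.2 names three reasons and is silent on others, such as withdrawal of consent.
- *That Day 21 is estimated only in people who tolerated dose 1 and came back.* Everyone with a Day 21 titre came back, whichever rule applies.
- *That completion means Day 228, so Per Protocol membership is unknown at the interim report* ("An interim clinical study report analyzing safety and immunogenicity at 42 days post-vaccination will be completed") *and could change later.* Section 5.1 does call Day 228 the end of study, so the literal reading is tempting. But the visit-specific sentences in 11.2.1.3 do not require attendance at Day 228, and 7.1.2 itself speaks of completing through Day 42. What stands is that the wording is loose and that violations have no cut-off by visit.
- *That one exclusion decides the 70% seroprotection criterion.* 8/12 = 66.7% does become 8/11 = 72.7% if a non-responder is removed, but it becomes 7/11 = 63.6% if a responder is. Section 8.2 does not tie the criterion to Day 21.
- *That the Full Analysis Set must be reported at every time point.* That would be a preference set against the choice stated in 11.2.2, not the correction of an error.

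**Conclusion.** The contradiction holds. A subject with valid Day 0 and Day 21 titres who leaves between Day 21 and Day 42 for a reason named in 7.1.2 is included by 11.2.1.2 and by the Day 21 sentence of 11.2.1.3, and excluded by 7.1.2. Following 7.1.2 would condition a planned secondary comparison on later dropout.

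The size cannot be fixed from the Protocol. If dropout is unrelated to titre, the cost is precision alone. If it is related, the assumed rates above shift a 60% seroprotection rate by about 3 points in either direction. These figures rest on assumed dropout and response rates, and the test example on chosen counts.

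This is a consistency and bias repair to a secondary endpoint. The primary safety analysis, done on all treated subjects, and the statement in 11.3 are unaffected.

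**What to change.** 1. In 7.1.2, delete the exclusion, or limit it to samples that cannot be tested, and refer to section 11.2 for who is analysed.
2. In 11.2.1.3 and the Synopsis, replace the completion requirement with a rule by visit. Day 21: dose 1 received, Day 0 and Day 21 titres, and no major violation up to Day 21. Day 42: both doses received, Day 0 and Day 42 titres, and no major violation up to Day 42.

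Both changes are to Protocol wording. They need no added subjects, samples or assays, and the sera in question are already to be assayed. They should be made before any titres are analysed.
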